## Abstract

**Background:**

Low back pain (LBP) is by far the most prevalent and costly musculoskeletal problem in our society today. Following the recommendations of the Multinational Musculoskeletal Inception Cohort Study (MMICS) Statement, our study aims to define outcome assessment tools for patients with acute LBP and the time point at which chronic LBP becomes manifest and to identify patient characteristics which increase the risk of chronicity.

**Methods:**

Patients with acute LBP will be recruited from clinics of general practitioners (GPs) in New Zealand (NZ) and Switzerland (CH). They will be assessed by postal survey at baseline and at 3, 6, 12 weeks and 6 months follow-up. Primary outcome will be disability as measured by the Oswestry Disability Index (ODI); key secondary endpoints will be general health as measured by the acute SF-12 and pain as measured on the Visual Analogue Scale (VAS). A subgroup analysis of different assessment instruments and baseline characteristics will be performed using multiple linear regression models.

This study aims to examine

1. Which biomedical, psychological, social, and occupational outcome assessment tools are identifiers for the transition from acute to chronic LBP and at which time point this transition becomes manifest

2. Which psychosocial and occupational baseline characteristics like work status and period of work absenteeism influence the course from acute to chronic LBP

3. Differences in outcome assessment tools and baseline characteristics of patients in NZ compared with CH.

**Discussion:**

This study will develop a screening tool for patients with acute LBP to be used in GP clinics to access the risk of developing chronic LBP. In addition, biomedical, psychological, social, and occupational patient characteristics which influence the course from acute to chronic LBP will be identified. Furthermore, an appropriate time point for follow-ups will be given to detect this transition. The generalizability of our findings will be enhanced by the international perspective of this study.

**Trial registration:**

[Clinical Trial Registration Number, ACTRN12608000520336]

## Background

Low back pain (LBP) is the most prevalent and costly musculoskeletal disease, potentially leading to permanent disability [1,2]. For economically advanced societies a lifetime prevalence of LBP of up to 80%, an annual prevalence of up to 60%, and a point prevalence of up to 40% is estimated [3]. The natural course of LBP is self-limiting whereas an estimated 10% of patients develop chronic LBP as defined by duration of more than 12 weeks [4,5]. Though chronic LBP affects only a small group of patients, it is a high socioeconomic burden exceeding the treatment of acute LBP significantly [6]. About 30% of these costs are direct costs caused by medical treatment, whereas 70% are attributable to indirect costs e.g. loss of production [2].

Hence, it is of high importance to detect patients at risk of developing chronic LBP at an early stage as well as to identify modifiable risk and protective factors [7]. Evidence and outcome-based research is needed to provide information on the appropriate assessment of patients with acute LBP. To identify these patients, prognostic factors of chronic LBP must be known. According to the biopsychosocial model the influence of various factors in addition to severity of LBP has to be taken into account [8,9].

Guidelines already exist for the management of acute LBP [10], but some of the main questions in acute LBP – which assessment tools are the best identifiers for patients at risk for the transition from acute to chronic LBP and at which time point this transition takes place – are not clearly answered. Chronic LBP is defined as LBP lasting longer than 12 weeks [11]. Furthermore, there are inconsistent findings on cross-country differences in commonly used patient outcome assessment tools and baseline characteristics [12-15].

Although screening instruments are not routinely used in medical practice they can help to detect prognostic factors in the course of LBP. They should consist of internationally accepted core outcome measures e.g. as recommended by the MMICS Statement and should be validated on a multinational level [16]. A recent review on screening instruments for the identification of prognostic factors for chronicity in patients with LBP reported that psychological and occupational factors have the highest reliability in predicting an unfavourable outcome [17]. Therefore, in this study protocol we focus on these factors in the design of a new comprehensive screening instrument.

## Methods

### Research plan

#### Objectives

This study aims to identify outcome assessment tools of patients with acute LBP which includes defining patient characteristics at baseline to allow the identification of patients at risk of developing chronic LBP [7,18-28] and at which time the chronicity becomes manifest [29-33]. This study will be undertaken in cohorts of patients in both New Zealand (NZ) and Switzerland (CH) to establish any similarities and differences between them [12-15].

#### Hypotheses

Three hypotheses will be examined:

1. Specific biomedical, psychological, social, and occupational outcome assessment tools are identifiers for the transition from acute to chronic LBP at a time point between 3 and 12 weeks.

2. Specific psychosocial and occupational baseline characteristics like work status and period of work absenteeism influence the course from acute to chronic LBP.

3. There are differences in patient outcome assessment tools and baseline characteristics between patients in NZ and CH, e.g. in disability compensation systems.

#### Study design

In this two arm cohort study, patients will be recruited from GP clinics in NZ and CH. Participants will be assessed directly after attending their GP for LBP treatment for the first time or for recurrent LBP after a pain free period of at least 6 months (T0) with follow-up at 3, 6, and 12 weeks, and at 6 months (T1-4). 6 months are the cut-off point in follow-up as longer follow-ups may incorporate additional errors affecting the identification of predictors.

The study protocol has been approved by the Lower South Regional Ethics Committee (LRS/08/03/008).

#### Inclusion and exclusion criteria

We defined broad inclusion criteria to ensure that the spectrum of patients represents the spectrum seen in routine settings: consecutive patients attending a GP clinic for acute LBP in Otago and Waikato districts, NZ and German speaking CH for a first time or after a pain free period of at least 6 months; a minimum age of 18 years at the time visiting a GP; a maximum age of 65 years; a good understanding of English or German; and a signed consent, are required.

Exclusion criteria are: chronic LBP (defined as LBP continuing for more than 12 weeks at time of first visit to GP) [11,30]; specific LBP (infection, tumour, osteoporosis, ankylosing spondylitis, fracture, deformity, inflammatory process, cauda equina syndrome) [10]; comorbidity that determines overall well-being (e.g. painful disabling arthritic hip joints); pregnancy; expected loss to follow-up (e.g. due to moving from the district); and unwillingness to complete questionnaires (Table 1).

**Table 1 T1:** Inclusion and exclusion criteria

**Inclusion criteria**	**Exclusion criteria**
1. Patients attending GP clinic with acute LBP	1. Chronic LBP
2. Age 18–65 years	2. Specific LBP
3. Good understanding of English (NZ) or German (CH)	3. Comorbidity determining overall well-being
4. Written consent	4. Pregnancy
	5. Expected loss to follow-up
	6. Unwillingness to complete questionnaires

### Outcome assessment

#### Demographic and baseline characteristics

The following demographic, biomedical, psychological, social, and occupational factors will be assessed at baseline according to the recommendations of the MMICS Statement:

- Gender [34,35]

- Age [32,36-38]

- BMI

- Ethnicity

- ODI [39,40]

- Acute SF-12 [41]

- Quality and intensity of LBP (SF-McGill including VAS) [42-44]

- LBP history (duration and recurrence) [45-48]

- Radiating leg pain below the knee

- Lifestyle factors (exercise, smoking, alcohol consumption) [49-52]

- Depression (modified self-rating depression scale by Zung ZUNG) [53,54]

- Somatisation (Modified Somatic Perceptions Questionnaire MSPQ) [55]

- Fear avoidance beliefs (Fear Avoidance Beliefs Questionnaire FABQ) [56-58]

- Pain catastrophizing (Pain Catastrophizing Scale PCS) [59]

- Marital/relationship status

- Social support

- Educational status

- Employment/work status

- Job satisfaction [35,60-62]

- Job control [35,63]

- Work stress factors [61,62,64-67]

- Belief that work has caused LBP [68-70]

- Duration of work-absenteeism [9,71-73]

- Reasons for not working

- Disability compensation status [74-79]

- Patients' expectations on return to work [80-82].

#### Outcome measures

ODI, acute SF-12, and VAS pain score are among the most frequently used outcome assessment measurements of LBP. All of them are valid and reliable. In this study of outcome predictors, the primary endpoint for chronicity is ODI. Key secondary endpoints are acute SF-12 and VAS pain score.

Other secondary outcomes that will be collected by patient self-assessment as recommended by the MMICS Statement are: reduction in normal activities due to LBP; health care utilization including treatment received and referral as provided by the Accident Compensation Corporation (ACC) and GPs; medication [83]; modified self-rating depression scale by Zung (ZUNG); Modified Somatic Perceptions Questionnaire MSPQ (MSPQ); Fear Avoidance Beliefs Questionnaire (FABQ); Pain Catastrophizing Scale (PCS); patient satisfaction with condition and care; return to work (RTW); and sick leave over the last week.

### Data management

#### Database

Patient data will be stored at a central database at the University of Otago (UoO), Dunedin, in strictly anonymised fashion. Data will be analysed in cooperation with a statistician in the Department of Preventive and Social Medicine, Dunedin School of Medicine. Data will be double entered and cleaned before use.

### Statistical analysis

#### Multivariate identification of predictors for chronicity

Changes in primary and secondary endpoints between baseline data and different time points of follow-up will be analysed by multiple linear regression models. Patients with chronic LBP at 6 months follow-up will be compared with patients without chronic LBP at the same time point.

Patients with chronic LBP in this study are defined as patients with an ODI score without improvement by a Minimal Clinically Important Difference (MCID) of 10 ODI points between T0 (attending the GP for the first time or after a pain free period of at least 6 months) and T4 (6 months follow-up) [84-87].

An analysis of different assessment instruments and baseline characteristics will be performed to find appropriate scores or patient characteristics to identify patients at risk to develop chronic LBP. Different patient assessment tools will be allocated to the following four groups: demographic-biomedical, psychological, social, and occupational risk group [88]. We aim to detect at least one assessment instrument in each group which identifies patients at risk.

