#### Identification of time of chronicity

In a second step, a subgroup analysis on patients without chronic LBP will be performed to identify the time of follow-up (TX) where this patient group shows an improvement in ODI by at least the MCID. As patients with chronic LBP by definition of their condition don't show an improvement at TX, this follow-up is the most appropriate time point for detecting the transition from acute to chronic LBP in patients at risk.

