### Sample size/power calculation

#### Sample size considerations

Sample size considerations in clinical studies start from what is considered a MCID. In studies of chronic LBP, the ODI is commonly used as the main outcome measure, and a difference in 10 ODI points is considered clinically relevant. We will consider the sample size and power according to the MCID of ODI.

A minimum of 10 patients with chronic LBP are needed to produce stable estimates for each predicting variable. We will collect data on e.g. 20 potential predictive factors and screen these by logistic regression. If assuming we select four of these predictors for regression modelling, looking for an independent effect, then at least 40 patients with chronic LBP will be needed, 10 patients for each predictor.

We considered a series of scenarios for sample size calculations which resulted in an array of sample sizes between 200 and 800 patients necessary to ensure 80% power at a two-sided p of 0.05. If 5% of patients with acute LBP develop chronic LBP, 800 patients will have to be analysed. However, if 10% or 20% develop chronic LBP at 6 months follow-up only 400 and 200 patients respectively will be needed. Trends from our pilot study including 20 patients in Otago district, NZ show that an even smaller sample size might be sufficient – due to a rate of chronic patients of up to 30% in the pilot sample.

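### The 6-month outcome counts anyone without a 10-point ODI improvement as chronic, so a patient who starts below ODI 10 is chronic even after full recovery

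*Protocol article*

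**What the plan says.** Under Multivariate identification of predictors for chronicity, the protocol article defines chronic LBP for this study as "patients with an ODI score without improvement by a Minimal Clinically Important Difference (MCID) of 10 ODI points between T0" and T4, the 6-month follow-up. The next section, Identification of time of chronicity, gives the direction of the threshold: the non-chronic group is followed to the visit at which "this patient group shows an improvement in ODI by at least the MCID". A drop of exactly 10 points therefore counts as improvement.

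The definition sets no ODI level at T4, does not ask whether pain persists, and makes no exception for low starting scores. The eligibility text and Table 1 list no minimum ODI. Breadth is deliberate: "We defined broad inclusion criteria to ensure that the spectrum of patients represents the spectrum seen in routine settings".

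Elsewhere the same term is defined by duration. The Background says "Chronic LBP is defined as LBP lasting longer than 12 weeks", and the exclusion criteria remove "chronic LBP (defined as LBP continuing for more than 12 weeks at time of first visit to GP". The Background also attaches a rate to the duration meaning: "an estimated 10% of patients develop chronic LBP as defined by duration of more than 12 weeks".

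**The concern.** A change score measures improvement, whereas the study sets out to predict persistence. The two separate at both ends of the scale. A mildly disabled patient who recovers completely may have too little room to improve by 10 points. A severely disabled patient may improve by 10 points and remain badly disabled.

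The label is used in four places:

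- the comparison of chronic with non-chronic patients at 6 months;
- the screening tool that the study aims to produce from that comparison;
- the 40 chronic patients required in Sample size considerations;
- the non-chronic subgroup used to find TX, from which recovered patients with low starting scores would be missing.

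Baseline ODI is one of the listed baseline factors. Under this rule a low value produces the outcome by construction, so a tool built on the label could partly flag patients who started mild.

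**Working it through.** **Inputs from the protocol article.** The threshold is 10 ODI points (Sample size considerations: "a difference in 10 ODI points is considered clinically relevant"), and an improvement of at least that size counts. Classification is at T4. There is no baseline ODI minimum. The plan needs 40 chronic patients (4 predictors × 10 each), with scenario rates of 5%, 10% and 20%.

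**Assumption from outside.** The lowest possible ODI is 0. The article does not print this.

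**Step 1: the plan's own figures.** N = 40 / rate gives 40/0.05 = 800, 40/0.10 = 400 and 40/0.20 = 200. These match the article. The arithmetic is sound, so the difficulty lies in what is being counted.

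**Step 2: the floor.** Improvement = T0 − T4 ≤ T0.

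| T0 | Best possible T4 | Largest improvement | Can be non-chronic? |
|---|---|---|---|
| 4 | 0 | 4 | no |
| 8 | 0 | 8 | no |
| 9 | 0 | 9 | no |
| 10 | 0 | 10 | yes, only at T4 = 0 |
| 12 | 0 | 12 | yes, only at T4 ≤ 2 |

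Below 10 the label is fixed at entry. Just above 10 it requires near-complete recovery.

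**Step 3: the other end.** A patient going from 60 to 48 improves by 12 and is labelled non-chronic with an ODI of 48.

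**Step 4: possible size.** Let t be the true chronic rate and f the share starting below ODI 10, taken as independent of chronicity. Assume that every truly chronic patient is labelled chronic and that every other patient starting at 10 or above improves enough. Both t and f are assumed.

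Labelled rate = t + f(1 − t). False share = f(1 − t) / [t + f(1 − t)].

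For t = 10%:

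| f | Labelled rate | False share | True cases per 40 labelled |
|---|---|---|---|
| 2% | 11.8% | 15% | 34 |
| 5% | 14.5% | 31% | 28 |
| 10% | 19.0% | 47% | 21 |
| 20% | 28.0% | 64% | 14 |

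For the same values of f, the false share is 28%, 49%, 66% and 79% at t = 5%, and 7%, 17%, 29% and 44% at t = 20%.

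As an example in patient numbers, take 400 analysed patients with t = 10% and f = 5%. There are 400 × 0.10 = 40 true cases and 400 × 0.05 × 0.90 = 18 false ones. That is 58 labelled cases, and 18/58 = 31%.

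**Step 5: dependence on baseline severity.** Suppose baseline ODI follows a gamma distribution with SD 14 to 16 (assumed). With mean 35, f is 0.7% to 1.8%, and the false share at t = 10% is 6% to 14%. With mean 40, f is 0.1% to 0.4% and the false share is about 1% to 3%. The floor effect fades as patients start worse.

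**The case against.** The strongest defence is that the definition is openly operational. The article says it applies in this study, and it rests on an MCID with cited support that cannot be seen here. An MCID-based responder rule is a recognised choice. The duration wording in the exclusion criteria governs entry, when no change score exists, and the Background wording is general. This stands in part. A reader might infer that the definitions flatly contradict each other, but they serve different purposes. What remains is that one term carries two meanings and the article does not say how they relate. Declaring the rule does not remove the floor effect.

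Three further inferences go too far:

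- **That the study was sized for a different condition.** The sample size section gives conditional scenarios for chronic LBP at 6 months, framed around the ODI MCID. It never says that it takes its 10% from the Background. The definition behind the rates is unstated, which is not the same as wrong.
- **That the pilot rate of up to 30% is a product of this rule.** It corresponds to 6 of 20 patients, with an exact 95% interval of about 12% to 54%. That fits many explanations, and the article does not say which definition the pilot used.
- **That all analyses for hypotheses 1 and 2 depend on the label.** The same section also plans multiple linear regression of changes in the endpoints, which does not use it.

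The 60-to-48 example is partly a matter of preference, since a 12-point gain is a real improvement. It still shows that the label does not describe a patient's condition at 6 months.

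**Conclusion.** The point holds as a defect in a stated rule. With an ODI floor of 0 and no baseline minimum, every patient starting below ODI 10 is labelled chronic whatever happens. No other part of the article rescues such patients. This affects the chronic versus non-chronic comparison, the screening tool, the event count and the TX subgroup. The linear regression of endpoint changes is not affected in the same way.

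The direction is certain, but the size is not. The article gives no baseline ODI distribution, so the false shares above are illustrations. They range from roughly 1% of labelled cases if patients start severely disabled to well over half if many start mild and true chronicity is rare. They count only the floor effect. They exclude patients just above 10 who recover almost fully, and disabled patients labelled non-chronic. No firm rate for either can be drawn from the documents.

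**What to change.** 1. Add a pre-specified T4 status condition to the outcome, using the ODI level, VAS pain or both, so that a patient recovered at T4 is not counted as chronic whatever the change. The investigators should choose and justify the cut-off; the documents provide no basis for one.
2. Include baseline ODI in the model for the chronic outcome.
3. Keep the 10-point change rule as a sensitivity analysis, and report how many patients started below ODI 10 and how they were classified.
4. State how the outcome relates to the 12-week definition. A direct check against pain duration may need an extra item, because LBP duration is listed only among the baseline factors.
5. State which definition the 5%, 10% and 20% scenarios and the pilot rate use, and apply the same one to the 40-event count and the TX subgroup.

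ODI and VAS are already outcome measures, so items 1 to 3 need no new data. The cost is a revised endpoint definition, one extra analysis and possibly a lower event rate than the pilot suggested. In that case, the remark that a smaller sample might suffice should be reconsidered.

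### Chronic LBP is defined by the T0-to-T4 ODI change only, so patients who improved by 12 weeks and then relapsed are counted with those who never improved, and the premise of the time-of-chronicity analysis fails for them

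*Protocol article*

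**What the plan says.** Under Multivariate identification of predictors for chronicity, the protocol article gives its own rule for the label: those counted as chronic are "defined as patients with an ODI score without improvement by a Minimal Clinically Important Difference (MCID) of 10 ODI points". The two assessments that enter this change score are named in the same sentence: it runs "between T0 (attending the GP for the first time or after a pain free period of at least 6 months) and T4", where T4 is the last follow-up, at half a year. The comparison then rests on that label: "Patients with chronic LBP at 6 months follow-up will be compared with patients without chronic LBP at the same time point".

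Elsewhere chronic LBP is a matter of duration. Background has "Chronic LBP is defined as LBP lasting longer than 12 weeks", and the exclusion criterion is "chronic LBP (defined as LBP continuing for more than 12 weeks at time of first visit to GP").

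Study design schedules further assessments at 3, 6 and 12 weeks (T1 to T3). Hypothesis 1 places the transition to chronic LBP between 3 and 12 weeks.

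Identification of time of chronicity looks for the follow-up time TX at which the non-chronic patients have improved by the MCID. It then argues that patients with chronic LBP, by the very definition of their condition, have not improved at TX, and concludes that TX is the best time to detect the transition.

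**The concern.** The label uses two ODI values and sets no persistence condition. Two different courses meet it: no improvement by 10 points at any visit, and improvement at some or all of T1 to T3 followed by a return to within 10 points of baseline, or worse, at T4. Only the first clearly resembles pain that lasts or continues beyond 12 weeks.

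Three things depend on the label:

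- **The predictor analysis.** Predictors of persistence are estimated against an outcome that may also contain relapse.
- **The choice of TX.** It relies on labelled patients not having improved earlier, which the label does not guarantee.
- **The event count.** The 40 chronic patients behind the sample size may include fewer persistent cases.

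This is separate from the question of low baseline scores. A relapsing patient can have a high ODI at both T0 and T4, so a baseline floor or an absolute T4 threshold would not separate the two courses.

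**Working it through.** **1. What the definition constrains.** Let D1 to D4 be the ODI improvement from T0 to T1, T2, T3 and T4. The label is: chronic if D4 < 10. It places no limit on D1, D2 or D3. A patient with D3 ≥ 10 and D4 < 10 is labelled chronic.

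**2. What the TX argument needs.** It needs D < 10 at TX for every labelled patient. That follows from the label only if TX is T4. Hypothesis 1 looks for the transition between 3 and 12 weeks, that is T1 to T3, where the label says nothing. This contradiction needs no outside figure.

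**3. The article's own sample size.** Sample size considerations asks for 10 chronic patients per predictor and four predictors: 10 × 4 = 40 events. With N = 40 / rate:

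- 40 / 0.05 = 800
- 40 / 0.10 = 400
- 40 / 0.20 = 200

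The stated 800, 400 and 200 are reproduced exactly. These rates are rates of the labelled outcome at 6 months, so any relapsing patients are already inside them.

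**4. Persistent cases among the 40.** Let s be the share of labelled patients who relapsed. The document gives no value; 10% to 50% is an assumption. Persistent cases = 40(1 − s). N for 40 persistent cases = 40 / [rate × (1 − s)], rounded up.

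| s | Persistent among 40 | N at 5% labelled | N at 10% labelled | N at 20% labelled |
|---|---|---|---|---|
| 0 | 40 | 800 | 400 | 200 |
| 10% | 36 | 889 | 445 | 223 |
| 20% | 32 | 1000 | 500 | 250 |
| 30% | 28 | 1143 | 572 | 286 |
| 50% | 20 | 1600 | 800 | 400 |

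**5. Direction of bias in an odds ratio.** Assumptions, none from the document: a binary predictor present in half the patients, a true odds ratio of 2 for persistence, and an odds ratio for relapse of 1 to 3. The labelled rate is 10%.

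- Persistent risks p0 and p1 solve (p0 + p1)/2 = 0.10(1 − s) with odds ratio 2.
- Relapse risks q0 and q1 solve (q0 + q1)/2 = 0.10s with the relapse odds ratio.
- The observed odds ratio compares p1 + q1 with p0 + q0.

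Example with s = 30% and relapse odds ratio 1: p0 = 0.0481, p1 = 0.0919, q0 = q1 = 0.03. The labelled risks are 0.0781 and 0.1219, and the odds ratio is (0.1219/0.8781) / (0.0781/0.9219) = 1.64.

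| Relapse OR | s = 10% | s = 20% | s = 30% | s = 50% |
|---|---|---|---|---|
| 1 | 1.87 | 1.75 | 1.64 | 1.43 |
| 1.5 | 1.96 | 1.92 | 1.88 | 1.78 |
| 2 | 2.03 | 2.05 | 2.06 | 2.08 |
| 3 | 2.11 | 2.22 | 2.33 | 2.55 |

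A predictor unrelated to relapse is attenuated. One equally related to relapse is almost unchanged. One more strongly related to relapse is inflated.

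**The case against.** The strongest defence is that the article openly sets a study-specific definition and compares status at a fixed 6-month follow-up, which is a legitimate prognostic outcome. It cites sources for the definition that are not available here. T1 to T3 are not ignored altogether either: changes from baseline to the different follow-up times are to be modelled by linear regression. All of this stands, and for that reason the T0-to-T4 definition need not be abandoned. It does not rescue the TX argument, which attributes to the definition something the definition does not contain.

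A second objection is that building T3 into the outcome creates circularity, because hypothesis 1 examines assessment tools in the 3 to 12 week window. This also stands, and it favours a sensitivity analysis over a new primary definition.

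Some stronger readings are tempting but unsupported:

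- **That the label rests on the T4 form alone.** It is a change from T0. A patient with a milder flare, whose T4 score is still 10 or more points below T0, is not labelled chronic.
- **That every predictor is diluted.** The last table shows attenuation, no material change or inflation, depending on how the predictor relates to relapse.
- **That these patients have new episodes, to be expected because recurrent LBP is admitted.** Entry is allowed "for recurrent LBP after a pain free period of at least 6 months", a gap that nobody recovering after T0 could complete by T4. Relapse or fluctuating course is the accurate term, and the article gives no rate for it.
- **That the 5%, 10% and 20% scenarios are rates of persistent pain to which relapses should be added.** They are rates of the labelled outcome.

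**Conclusion.** The point holds in a limited form. From the text alone, the T0-to-T4 label can combine relapsing with persistent patients, it does not match the duration concept in Background and in the exclusion criteria, and the claim that chronic patients cannot have improved at TX is untrue for T1 to T3. For relapsing patients, the inference that TX detects the transition fails.

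The numerical effect cannot be fixed, because the relapse share and the predictors' relation to relapse are not given. Under the assumed shares of 10% to 50%, 36 to 20 of the 40 planned events would be persistent cases. Odds ratios could move either way: with a true value of 2 and a 10% labelled rate, the illustrated range is 1.43 to 2.55. The correction is worth making because it is cheap and decides whether the study can speak of persistence or only of status at 6 months.

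**What to change.** **Definition (Multivariate identification of predictors for chronicity).** Either keep the T0-to-T4 definition and say that it describes status at 6 months, or state that chronic means sustained non-improvement. In either case, split the T4-chronic group into two classes that do not overlap:

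- persistent: improvement below 10 points at both T3 and T4;
- relapsing: improvement of 10 points or more at T3 but not at T4.

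A patient who improved at T1 or T2 but not at T3 or T4 then falls in the persistent class only.

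**Sensitivity analysis.** Prespecify a repeat of the predictor analysis with persistent cases against patients not chronic at T4. Leave relapsing patients out of both cases and controls in that analysis, and report them separately.

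**Identification of time of chronicity.** Delete the claim that non-improvement at TX follows from the definition. Report instead the observed proportion of T4-chronic patients who had improved by 10 points or more at each of T1, T2 and T3, and use it in choosing TX.

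**Cost.** No new data are needed, because the T1 to T3 forms are already scheduled and the TX analysis already needs their ODI. The persistent analysis will have fewer events, so the number expected should be stated. Missing T3 forms need a rule. T3 ODI must not be assessed as a predictor of an outcome that contains it.
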